## **STUDY ORGANIZATION**

### *Institutional Participation and Qualified Investigator (QI) responsibilities*

The protocol will be conducted at six Ontario sites: London Regional Cancer Program, Princess Margaret Cancer Centre and Toronto Sunnybrook Cancer Centre, St. Joseph's Healthcare Hamilton, Ottawa Regional Cancer Centre and Thunder Bay Regional Cancer Centre. One Qualified Investigator (QI) will oversee the registry study at each clinical centre. Co-investigators at each Centre should include at a minimum a dually qualified nuclear medicine/radiology physician (alternatively separate nuclear medicine and radiology physicians) and urologist. The QI undertakes to enroll patients on the registry study in accordance with this protocol, ICH guidelines for Good Clinical Practice and the applicable national regulations and local REB requirements. The QI works with the co-investigators and may appoint other individuals, as he/she deems appropriate to assist in the conduct of the study. All appointed designates will be listed and provided to the sponsor. The appointed designates will be supervised by and under the responsibility of the QI. For the purpose of ensuring compliance with the clinical trial protocol, ICH GCP and applicable regulatory requirements, the QI agrees to permit study monitoring/auditing by or on the behalf of the sponsor, the institution and inspection by applicable regulatory authorities. The Investigator agrees to allow the auditors/inspectors to have direct access to his/her study records for review.

### **Registry Coordination**

The Sponsor is responsible for the overall study management including finance and contracts, implementation of the study protocol logistics, patient allocation, data management, quality assurance. The Sponsor is responsible for monitoring study execution, particularly with regard to methodological aspects and ensuring each clinical centre adheres to the study protocol. There will be a data query process, visit management tracking and SAE tracking to ensure data is complete, accurate, of high quality and is reported/submitted according to required timelines. An in-house Ethics & Regulatory Affairs Officer will complete and submit the initial application to OCREB and facilitate the other centres' applications, ensuring required start-up documentation is obtained from each clinical centre prior to centre activation.

### **Data Safety Monitoring Committee**

The investigational imaging agent, [18F]DCFPyL has undergone human testing with no adverse toxicity noted. As such a formal Data Safety Monitoring Committee will not be arranged for this study. In the case of any AEs, SAEs of grade 3 or higher attributable to the investigational imaging, accrual to the study will be suspended and the case in question reviewed by the Principal Investigators to identify any contributing or remedial causes before continuing accrual.

## **STATISTICAL CONSIDERATIONS**

### *Statistical Analyses*

Descriptive statistics will be used to summarize patient, tumour and treatment characteristics, along with endpoints. The primary endpoint will be described using proportions, along with a 95% exact confidence interval, and tested using an exact test of proportions. Secondary endpoints will be summarized using descriptive statistics, along with confidence intervals as appropriate. All tests and confidence intervals will be two-sided and statistical significance will be defined at the  $\alpha=0.05$  level. No statistical adjustments will be performed for multiple testing; however, appropriate caution will be taken when inferring results from this study due to the fact that multiple tests will be

performed. Given the sample size, all tests and confidence intervals will be based on exact or non-parametric methods.

#### *Null hypothesis*

PSMA PET will detect sites of recurrence at the time of early biochemical failure after prior prostatectomy at a rate equal to that of conventional imaging.

#### *Alternative hypothesis*

PSMA PET will detect sites of recurrence at the time of early biochemical failure with a higher frequency as compared to conventional imaging.

#### *Sample size calculation*

Conventional imaging can be expected to detect recurrent disease in under 10% of men at the time of biochemical failure. Detection of sites of disease in 30% or more men would be considered a clinically meaningful improvement in performance compared to conventional imaging. For  $H_0=0.10$  and  $H_A=0.30$ ,  $\alpha=0.05$  and  $b=0.10$ , with a two-sided, one-sample test of proportion a minimum sample size of 56 men will be required in each cohort for initial registry analysis. Assuming approximately a 15% dropout a total of at least 65 men per cohort will be necessary or minimum 455 men overall for initial registry analysis. Those cohorts demonstrating positive results will remain open for further access while further regulatory and funding approval is sought.

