**Cohort 6.** While many men receive prostatectomy as their primary therapy for prostate cancer, radiotherapy (external beam radiotherapy, brachytherapy or combinations together or with ADT therapy) is the primary treatment for men either unfit for surgery or for men who wish to avoid an invasive procedure or the potential side effects of surgery. In men receiving primary radiotherapy, biochemical failure may be seen in up to 25-30% of men. Particularly in those men with localized disease at initial treatment, accurate restaging may facilitate the selection of men for local salvage therapy such as salvage prostatectomy or other local salvage interventions such as cryotherapy, high intensity focused ultrasound or repeat radiotherapy (typically brachytherapy). The prospective PICs study (NCT02793284), evaluated 18F-DCFPyL in the radio-recurrent setting and demonstrated the ability to detect extra-prostatic recurrence in approximately twice as many men (38% vs. 18%) compared to conventional imaging) and changed management based on conventional imaging in approximately half of men (personal communication). This cohort will evaluate 18F-DCFPyL to provide further validation of its performance in this patient population and provide continued access for this patient population now that the PICs study has concluded.

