## **STUDY DESIGN – PHASE 2 REVISION**

During Phase I of the PREP protocol, all patients were required to have conventional imaging (computed tomography and bone scan) either negative or demonstrating oligometastatic disease. Based on an analysis of the first 400 patients accrued, the majority of patients (76%) had negative conventional imaging, with 24% had oligometastatic disease. Overall PSMA PET/CT detection rates of new lesions were similar among patients with negative conventional imaging (59%) versus oligometastatic disease on conventional imaging (63%). There were 12% of patients who had extensive disease on subsequent PSMA PET/CT with the rest of patients having negative scans or oligometastatic disease. Of these patients half (6%) had negative conventional imaging and half had oligometastatic

disease on conventional imaging (patients who had extensive metastatic disease on conventional imaging were not eligible for participation in PREP). Given these findings, it would appear that conventional imaging is not providing additional value in terms of overall staging compared to PSMA PET/CT alone, although this conclusion is limited somewhat by the fact that patients with extensive disease were excluded from participation from the first Phase of PSMA PREP. Given the historical data suggesting low rates of positive conventional imaging at PSA levels (<10 ng/ml) where actionable (locally recurrent or oligometastatic) disease is most likely to be found (27, 28) it is reasonable to hypothesize that omission of conventional imaging as criteria for PSMA PET/CT should not materially affect the performance of the test. Omission of conventional imaging would save costs and also improve the efficiency of evaluating men as currently waits for conventional imaging can add weeks to months to the waiting time for accessing PSMA PET/CT as part of PREP. To investigate the hypothesis that conventional imaging is not adding to the information provided by PSMA PET/CT alone, PREP Phase 2 will retain the same study design as Phase I but will remove bone scan and computed tomography as criteria for entry into the study except for those patients with higher PSA (>10 ng/ml). Identical cohort sizes will be accrued in Phase 2 to permit comparison of detection rates with similar confidence intervals with and without conventional imaging. Transition to PREP Phase 2 will occur when overall accrual to PREP has exceeded 80% of target.

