### **Exclusion Criteria**

1. Prostate cancer with significant sarcomatoid or spindle cell or neuroendocrine small cell components
2. Extensive metastatic disease on conventional restaging (>4 sites unequivocally positive for disease). Unless PET/CT requested as part of Cohort 7.
3. Prior PSMA PET scan within 6 months of enrollment
4. Patient cannot lie still for at least 60 minutes or comply with imaging
5. Patients falling outside of Cohorts 1-6 where independent adjudication by CCO does not support participation in the Registry

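### The stated null is equality with conventional imaging, but the test is against a fixed 10% that the registry's own 24% contradicts, so rejection does not show that PET detects more

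*Protocol*

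**What the plan says.** - **Hypotheses** (Protocol, Null hypothesis and Alternative hypothesis). Under the null, PET detects sites of recurrence "at a rate equal to that of conventional imaging". Under the alternative it detects them more often.
- **Test** (Statistical Analyses; Sample size calculation). The primary proportion gets an exact confidence interval and an exact test: "All tests and confidence intervals will be two-sided and statistical significance will be defined at the" 0.05 level. The comparator is a constant, H0 = 0.10, because "Conventional imaging can be expected to detect recurrent disease in under 10% of men at the time of biochemical failure". The alternative is 0.30: "Detection of sites of disease in 30% or more men would be considered a clinically meaningful improvement in performance compared to conventional imaging". The stated size is "with a two-sided, one-sample test of proportion a minimum sample size of 56 men will be required in each cohort for initial registry analysis".
- **Consequence.** Cohorts with positive results are to stay open while approval is sought. What counts as positive is not defined.
- **Registry data** (Study Design – Phase 2 Revision). In the first 400 men, "the majority of patients (76%) had negative conventional imaging, with 24% had oligometastatic disease". Men with extensive disease on conventional imaging could not enter. PET detected new lesions in 59% of conventional-negative men and 63% of men with oligometastatic conventional imaging.
- **Outside figure** (Cohort 6 description). In an earlier study after primary radiotherapy, PET was reported to "detect extra-prostatic recurrence in approximately twice as many men (38% vs. 18%) compared to conventional imaging".
- **Later revisions.** Cohorts 2, 3 and 6 were enlarged to 369 evaluable men (425 accrued) for precision. Cohorts 1, 4, 5 and 7 stay at 65 under the original endpoint. Phase 2 repeats these sizes, and the 10% null was not revised.

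**The concern.** The hypothesis compares two imaging methods, but the test compares one of them with a number. The two agree only if 10% is a fair upper value for conventional imaging in the men studied. The Protocol's own figure from its first 400 men is more than twice that. A cohort could then give a significant result with a PET rate at or below the conventional rate reported for the registry. The 5% error rate would not apply to the claim actually made. At stake are the wording of the main conclusion and the size of the gain shown to regulators and funders.

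**Working it through.** **Inputs.** From Sample size calculation: H0 = 0.10, HA = 0.30, two-sided alpha 0.05, beta 0.10, n = 56, 15% dropout. From Sample Size Revision: n = 369 (425 accrued). From Study Design – Phase 2 Revision: 24% of 400 conventional-positive; PET new-lesion rates 59% and 63%. From the Cohort 6 description: 18%.

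**1. The plan's own figure.** With the variance taken at the alternative, n = (1.960 + 1.282)² × 0.30 × 0.70 / 0.20² = 55.2, rounded up to 56. Then 56 × 1.15 = 64.4, rounded up to 65, and 7 × 65 = 455. The sample size reproduces and is not in dispute.

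**2. The conventional rate in the registry.** 0.24 × 400 = 96, with exact 95% CI 19.9% to 28.5%. The value 10% lies well outside.

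**3. Rejection limits and their behaviour.** The limit is the smallest k with P(X ≥ k | n, 0.10) ≤ 0.025. At n = 56, P(X ≥ 10) = 0.049 and P(X ≥ 11) = 0.021, so k = 11. The last two columns give P(X ≥ k) when PET's true rate is 24% or 18%.

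| n | Reject from | As a rate | True rate 24% | True rate 18% |
|---|---|---|---|---|
| 56 | 11 | 19.6% | 0.82 | 0.43 |
| 65 | 13 | 20.0% | 0.81 | 0.39 |
| 369 | 50 | 13.6% | >0.999 | 0.99 |
| 425 | 56 | 13.2% | >0.999 | >0.99 |

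A minimum-likelihood two-sided p-value lowers the limit by one at n = 65 and n = 369. Every limit lies below 24%: results of 11 to 13 of 56, or 50 to 88 of 369, are significant yet under the pooled conventional rate.

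**4. What the benchmark does to the apparent gain.** PET found new lesions in 0.76 × 59% + 0.24 × 63% = 44.8% + 15.1%, about 60%. Against 10% the gain is 50 points; against 24% it is 36. The planned 30% is 20 points above 10% but only 6 above 24%. To show the sensitivity (not as a proposal): with a null of 24%, n = 56 needs 21/56 (37.5%), and power at 30% falls from 97% to 14%. At a true 60%, power exceeds 99.9% under either null.

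**5. Is a direct comparison feasible?** Phase 1 inclusion criterion 6 requires bone scan and CT, so each man has both results. The pooled figures imply PET-positive/conventional-negative 0.76 × 0.59 = 45%, and PET-negative/conventional-positive at most 0.24 × 0.37 = 9%. It is at most 9% because the 63% counts new lesions only. Exact McNemar power at n = 56, summed over the discordant count, is 97% for 45%/9%. For assumed splits it is 99% (40%/4%, that is 60% vs 24%) and 76% (25%/5%, that is 38% vs 18%).

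**6. Phase 2.** Phase 2 inclusion criterion 7 asks for conventional imaging only when PSA exceeds 10 ng/ml. Men at or below that value need not have a conventional result, so the stated null has no comparator in them.

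**The case against.** Several stronger readings are tempting, and the document does not support them.

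- **That a cohort can be called positive although PET found fewer men than conventional imaging did in that cohort.** The 24% is pooled, and the registry includes men on hormone therapy (Cohort 4) and men previously treated for oligometastatic disease (Cohort 5). No cohort-specific conventional rate is given, so 10% may be close to right in some cohorts.
- **That the significance test decides which cohorts stay open.** A positive result is undefined. If it means an observed rate of 30% or more, no positive cohort can fall below 24%; at a true 24% that would occur with probability 0.17 at n = 56 and 0.004 at n = 369. The Phase 2 sample-size section also keeps all cohorts open until every target is met.
- **That 18% is the right null for Cohort 6.** It counts extra-prostatic disease only and comes from another study by personal communication. Cohort 6 is now sized at 369, so the 0.43 at n = 56 does not describe it.
- **That Cohort 7 contains men with known extensive disease.** Phase 1 exclusion 2 carries the waiver "Unless PET/CT requested as part of Cohort 7", but inclusion criterion 6 still limits conventional imaging to four lesions with no such waiver. This is a contradiction to reconcile, not evidence that these men enter.
- **That 24% should become the new fixed null.** It is a mid-trial estimate from a sample cut off at four lesions, with its own uncertainty.

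The strongest general objection is that the error is remote: PET's pooled rate is about 60%, and Cohorts 2, 3 and 6 (3 × 425 = 1,275 of 1,535 men) are sized for estimation. That stands as to practical risk. It does not make a test against 10% a test of equality with conventional imaging.

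**Conclusion.** The concern holds in this limited form. The Protocol fixes a hypothesis about conventional imaging and a test against 10%, and its own 24% shows that these differ. Rejection from 19.6% (n = 56) or 13.6% (n = 369) does not establish that PET exceeds conventional imaging. At a true PET rate of 24%, rejection has probability 0.82 and above 0.999. These figures assume an equal-tailed exact test and use the pooled 24% as a reference, not as any cohort's rate. The likelihood of a wrong verdict is low if individual cohorts resemble the pooled 60%. The lasting harm is an unsupported conclusion and a gain overstated by about 14 points (50 against 36).

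**What to change.** - **Phase 1.** In Statistical Analyses through Sample size calculation, replace the test against 10% with an exact McNemar comparison of PET-positive and conventional-positive status in the same men, by cohort, with the paired difference and 95% CI.
- **Equivocal conventional results.** Count them as negative, with a sensitivity analysis counting them as positive.
- **Limits to state.** The sample excludes men with more than four conventional lesions, which tends to favour PET. The scans may lie up to 3 + 6 = 9 months apart (imaging up to 3 months before registration, PET up to 6 months after), so tabulate the interval.
- **Phase 2, PSA of 10 ng/ml or below.** Report the detection rate with its exact CI and make no test against conventional imaging.
- **Reconcile.** Tie a positive result to the paired comparison and square it with the open-accrual rule in the Phase 2 sample-size section. Reconcile the Cohort 7 waiver in Phase 1 exclusion 2 with inclusion criterion 6.

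The cost is wording in the statistical section and one table per cohort from data already required for eligibility. The price is a less flattering contrast and no formal test against conventional imaging for Phase 2 men at or below the PSA limit.

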#### *Sample Size Revision, Cohorts 2, 3, 6*

A recent meta-analysis by Perera et al (27) of 37 studies and 4790 patients focused on the performance of 68Ga-PSMA in primary staging as well as restaging of men with biochemical failure after radical prostatectomy or radiotherapy. They found a detection rate of 0.48 (PSA 0.2-0.49) to 0.97 (PSA>2) depending on the PSA at time of imaging following biochemical failure. In order to demonstrate that 18F-DCFPyL provides a similar detection rate as described by Perera et al for 68Ga-PSMA based agents, we will increase our sample size for cohorts 2, 3 and 6. To allow us to estimate the detection rate with a precision of +/-5% (with 95% confidence), assuming a detection rate of 60%, we will require 369 patients per cohort, 425 assuming a 15% dropout rate. With cohorts 1, 4, 5 and 7 remaining at 65 men each according to the original endpoint, this will result in a total sample size of 1535 men.

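### The 425 enrolled per cohort in cohorts 2, 3 and 6 leaves about 361 evaluable men, not 369, after 15% dropout, and the specified exact interval is about ±5.2 points, not ±5 (minor)

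*Protocol*

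**What the plan says.** The Protocol section on the sample size revision for cohorts 2, 3 and 6 sets a "precision of +/-5% (with 95% confidence") and does so "assuming a detection rate of 60" per cent. It concludes that "we will require 369 patients per cohort, 425 assuming a 15% dropout rate".

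The section Sample size calculation, which still governs cohorts 1, 4, 5 and 7, requires a minimum of 56 men for 0.10 against 0.30 at 90% power "with a two-sided, one-sample test of proportion". It then adds: "Assuming approximately a 15% dropout a total of at least 65 men per cohort will be necessary".

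The section Statistical Analyses fixes how the result will be reported: "The primary endpoint will be described using proportions, along with a 95% exact confidence interval". It adds that "all tests and confidence intervals will be based on exact or non-parametric methods".

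The section Sample Size Revision - PREP Phase 2 carries 425 and 65 forward unchanged. The Phase 2 design section justifies the identical cohort sizes by the similar confidence intervals they would give.

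**The concern.** Two steps in the derivation do not fit the rest of the plan.

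- **Dropout.** The enrolled number is obtained by adding 15% to the evaluable number. Dropout is a fraction of those enrolled, so the enrolled number has to be the evaluable number divided by 0.85. The shorter method always leaves too few men.
- **Interval.** The ±5 points is computed for a normal-approximation interval, but the interval to be reported is exact, and that is wider at the same sample size.

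The stated precision is the reason given for raising three cohorts from 65 to 425 men, and it is also the basis for the Phase 2 sizes. A reader who relies on it would expect slightly more than the design delivers.

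**Working it through.** **Inputs, all from the Protocol.** Detection rate 0.60, precision 0.05, 95% confidence, 369 evaluable, 425 enrolled and dropout 15% (Sample Size Revision, Cohorts 2, 3, 6). Rates 0.10 and 0.30, two-sided alpha 0.05, beta 0.10, 56 evaluable, 65 enrolled and dropout of about 15% (Sample size calculation). Exact tests and intervals (Statistical Analyses).

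**1. Reproducing the stated figures.**
- 369: 1.96² × 0.6 × 0.4 / 0.05² = 368.8, rounded up to 369. This is the normal-approximation formula.
- 56: (1.960 + 1.282)² × 0.3 × 0.7 / 0.2² = 55.2, rounded up to 56.
- 425: 369 × 1.15 = 424.35, rounded up to 425.
- 65: 56 × 1.15 = 64.4, rounded up to 65.

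All four reproduce, so the multiplication by 1.15 is the method used in both places.

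**2. Men left after 15% dropout.**
- 425 × 0.85 = 361.25, about 361, which is 8 below 369. The dropout that 425 can absorb is 1 − 369/425 = 13.2%.
- 65 × 0.85 = 55.25, about 55, which is 1 below 56. The dropout that 65 can absorb is 1 − 56/65 = 13.8%.
- Division would give 369/0.85 = 434.1, so 435, and 56/0.85 = 65.9, so 66. The total would be 3 × 435 + 4 × 66 = 1569, against the stated 3 × 425 + 4 × 65 = 1535.

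**3. Half-width of the 95% interval at about 60%, in percentage points.** Normal: 1.96 × √(0.24/n). Exact: Clopper-Pearson, half the distance between the limits, at the nearest whole count.

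| Evaluable n | Count | Normal | Exact limits | Exact half-width |
|---|---|---|---|---|
| 369 | 221 | 4.999 | 54.7 to 64.9 | 5.12 |
| 361 | 217 | 5.05 | 54.9 to 65.2 | 5.17 |

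The dropout slip costs 5.05 − 5.00 = 0.05 points. With the change of interval the total is 5.17 − 5.00 = 0.17 points. The exact interval misses 5.0 even if all 369 men are evaluable.

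**4. Size needed for an exact half-width of 5 points.** This is first reached at 386 evaluable men when 0.6n is rounded to a whole count, or 387 when it is not. Enrolment would then be 386/0.85 = 454.1, so 455, or 387/0.85 = 455.3, so 456. Requiring each limit separately to lie within 5 points takes 398 evaluable, or 469 enrolled.

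**5. Consequence for the 65-man cohorts.** Exact binomial test, 0.10 against 0.30, upper tail at most 0.025:
- n = 56: reject at 11 or more detections, power 97.1%.
- n = 55: reject at 11 or more detections, power 96.6%.

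Both are far above the planned 90%.

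**The case against.** The strongest reply is that nothing of practical weight changes.

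- **Rounding.** To whole points, as the protocol writes its precision, 5.05 and 5.17 are both ±5. This stands as a statement of size. It does not make 361 equal to 369.
- **Custom.** Sizing with the normal formula and reporting an exact interval is common, and the protocol does not say that the 5 points is an exact half-width. That is fair, but the protocol also does not say that it is an approximation, and it commits all intervals to exact or non-parametric methods.
- **Planning uncertainty.** The true rate matters more than 8 men. With 361 evaluable, the exact half-width is 5.28 points at a rate of 50%, 5.04 at 65% and 4.85 at 70%. No decision rule turns on 5.0. This stands, and it is why the point is minor.
- **Continued accrual.** Cohorts stay open while any cohort is short of target, so most may exceed 425. This also stands in part, but the last cohort to fill has no guaranteed surplus.
- **Wording for the 65-man cohorts.** The protocol says approximately 15% and at least 65, and one man is missing. This stands fully.

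A reader might infer that the 65-man cohorts are underpowered, or that the registry fails its precision aim in a way that matters. The documents support neither: exact power at 55 men is 96.6%, and the interval is wider by less than a fifth of a point.

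**Conclusion.** Wrong as written, and minor. For cohorts 2, 3 and 6, 425 enrolled does not yield the required 369 evaluable men at the stated dropout. The stated ±5 points is also not the half-width of the interval that will be reported. The reported interval would be about ±5.2 points.

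This rests on a detection rate of 60%, dropout of exactly 15%, accrual stopping at target, and a Clopper-Pearson reading of the exact interval. The same slip in the 65-man cohorts is immaterial.

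A reader might also take 435 enrolled as the full correction. It is not: it restores 369 evaluable men, at which the exact half-width is still 5.12 points.

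**What to change.** In Sample Size Revision, Cohorts 2, 3, 6, and for the same targets in Sample Size Revision - PREP Phase 2, state that 425 enrolled with 15% dropout gives about 361 evaluable men per cohort. Add that the exact 95% interval is then about ±5.2 points at a detection rate of 60% (±5.05 by the normal approximation). In Sample size calculation, a note that 65 enrolled gives about 55 evaluable men, with exact power still near 97%, is enough.

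This is a change of text only. It adds no men and leaves the 1535 total as it is.

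If the sponsor prefers to change the targets, the text should say what each buys. Enrolling 435 and 66 restores 369 and 56 evaluable men for 1569 − 1535 = 34 more men per phase, with ±5 points then labelled as a normal approximation. An exact half-width of 5 points would need about 455 enrolled in each of the three cohorts, which is 3 × 30 = 90 more men per phase. The size of the shortfall does not call for either.
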